### Sample screening and cRCT

We will include 160 high-risk friendship dyads who are primarily characterized by high levels of co-rumination within their daily interaction patterns. “High risk” is defined on the dyadic level and implies that at least one of the two girls of one friendship dyad, or both girls, should have a score of at least one standard deviation above the mean co-rumination screening score (see below). Therefore, approximately 1000 girls of approximately 100 8th and 9th classes of Koers VO schools with written informed consent will be screened on maladaptive co-rumination through the Co-rumination Questionnaire-Short [21]. All girls will receive an email with a secured link to the online questionnaire and a request to complete the questionnaire within 1 week. A first reminder will be sent after 1 week, a second reminder after 2 weeks and finally, the research team will contact the girls by phone with a final prompt to complete the questionnaire.

After completing the screening procedure, all dyads with at least one of the two girls with a score of at least one standard deviation above the overall mean co-rumination screening score will be eligible for inclusion in the cRCT. Finally, 160 Dutch girls from age 13 to 15 years old with high levels of maladaptive co-rumination and their good or best friend from age 13 to 15 years old within the same secondary school (*n* = 320 girls; 160 dyads) will be included in the cRCT. In anticipation of 20% dropout, 16 dyads will be placed on a waiting list.

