Specifically, discrete-time survival analysis (DTSA) will be used to investigate whether girls in the intervention group have a later onset of depression symptoms or disorder compared to girls in the control arm. Note that this hypothesis focuses on individual rather than dyadic outcomes. To adjust for individuals clustered within dyads, we will adjust the standard errors using a sandwich estimator [104]. Furthermore, a prospective change, Actor-Partner Interdependence Model (APIM) will be used to investigate whether dyads in the intervention condition will experience less dyadic depression contagion compared to dyads in the control arm from T0 to 1-year after follow-up. We will use multi-group comparisons to test whether contagion effects are less strong in the intervention arm compared to the control arm.

Hypothesis 3 “Girls in the intervention group will demonstrate (a) less anxiety problem talk and will have a (b) later onset of anxiety symptoms or a later onset of anxiety disorder and (c) less dyadic anxiety contagion during the intervention period, immediately after the intervention period, and after 1-year follow-up, relative to girls in the control condition” will be tested using multi-level LGM, DTSAs, and multi-group APIM, respectively.

Specifically, a multi-level LGM with intervention arm as the exogenous predictor variable and growth rate of anxiety problem talk as the outcome variable will be used to test whether girls in the intervention arm demonstrate less anxiety problem talk compared to girls in the control arm. Furthermore, DTSAs of anxiety symptom onset and anxiety disorder onset with intervention condition as an exogenous predictor will be used to test whether girls in the intervention group have a later onset of anxiety symptoms or disorder compared to girls in the control arm. Lastly, a multi-group (i.e., intervention versus control condition) APIM will be used to investigate whether dyads in the intervention condition will experience less anxiety contagion compared to dyads in the control arm from T0 to 1-year after follow-up.

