All analyses will be conducted in structural equation modeling program Mplus (v 8.7 or higher; [106]). Model fit will be determined using the comparative fit index (CFI; critical value ≥ 0.95), the root mean square error of approximation (RMSEA; critical value ≤ 0.06), and the standardized root mean square residual (SRMR; critical value < . 08; [107]). When appropriate, standard errors will be adjusted for clustering of dyads within schools using a sandwich estimator [104]. For hypotheses that include mediation analysis (hypothesis 1 and 5), we will use 10,000 bootstrap resamples with replacement and bias-corrected 95% confidence intervals to test these indirect effects [108]. When appropriate, differences in (indirect) pathways between the intervention and the control arm will be estimated using the DIFFtest option in Mplus (when using the weighted least squares means and variance adjusted (WLSMV) estimator) or the Satorra Bentler chi-square difference test [109]; when using the maximum likelihood estimator with robust standard errors (MLR) estimator).

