### Handling of protocol non-adherence and missing data

The way the questionnaires are administered online makes it impossible to skip a question. Participants who do not complete a questionnaire will receive one or more reminders. Missing data during observations is also not possible. Missing data during the follow-up period (e.g., due to unavailability during a certain measurement wave or due to dropout) will be handled using Full Information Maximum Likelihood (FIML) estimation.

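### The article says all missing follow-up data are handled by FIML, yet allows WLSMV, under which FIML cannot operate; which models are affected is left open

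*Protocol article*

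**What the plan says.** Two neighbouring parts of the protocol article bear on this.

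- *Handling of protocol non-adherence and missing data* names one method. It covers missed waves and dropout alike: "Missing data during the follow-up period (e.g., due to unavailability during a certain measurement wave or due to dropout" is the missingness described, and it "will be handled using Full Information Maximum Likelihood (FIML) estimation". No model, outcome or estimator is exempted.
- *Statistical methods for primary and secondary outcomes* fixes the software ("All analyses will be conducted in structural equation modeling program Mplus") and then sets out how pathways are compared between arms: "When appropriate, differences in (indirect) pathways between the intervention and the control arm will be estimated using the DIFFtest option in Mplus", this being the route "when using the weighted least squares means and variance adjusted (WLSMV) estimator". The alternative is a Satorra-Bentler difference test "when using the maximum likelihood estimator with robust standard errors (MLR) estimator".

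The article does not say which hypothesis or outcome goes with which estimator. For onset it says that "discrete-time survival analysis (DTSA) will be used to investigate whether girls in the intervention group have a later onset of depression symptoms", without naming an estimator. No missing-data method is given for a model fitted with WLSMV.

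On the amount of missing data, *Sample screening and cRCT* says: "In anticipation of 20% dropout, 16 dyads will be placed on a waiting list".

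**The concern.** FIML is a property of maximum likelihood estimation. It uses each girl's observed waves, so dropout may depend on her earlier observed scores without biasing the estimates. WLSMV first estimates thresholds and correlations from the cases available for each variable or pair, and then fits the model to those by weighted least squares. Missingness may then depend on exogenous covariates such as arm, but not on earlier values of the outcomes. One model cannot have both properties.

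Dropout linked to symptoms is plausible here. The trial is open label, only the HFPM arm has 14 sessions and daily app use, and withdrawn girls are not followed up. Reasons for leaving could therefore differ by arm. If they do, an available-case analysis can shift the arm contrast while the report says that FIML dealt with the missing data. Because the choice of estimator is open, the missing-data assumption would be settled by a decision made at analysis.

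**Working it through.** **Step 1: is there a conflict?** The missing-data section applies FIML to all missing follow-up data. The analysis section allows two estimators. MLR is likelihood-based and agrees with the FIML sentence; WLSMV is not and does not. An SAP that assigns estimators could make the WLSMV set small or empty, but for any model left in it the FIML sentence is untrue.

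**Step 2: which models could be affected?** The WLSMV clause concerns differences in pathways between arms.

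- The multi-group arm comparisons named are the actor-partner models for depression and anxiety contagion and the latent transition analysis (LTA).
- LTA and the joint LTA and survival model are mixture models, which need maximum likelihood.
- Discrete-time survival analysis (DTSA) is usually fitted by maximum likelihood.
- The actor-partner models would suit MLR if they use scale scores (CDI-2 total 0 to 56; six RCADS items scored 0 to 3).
- What remains is any model in which items or outcomes are declared categorical and WLSMV is chosen.

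**Step 3: how large could the effect be?** The plan has no figure of its own to reproduce on this point. From the documents: 20% dropout, and d = 0.35 as the smaller effect of interest. Assumed: a standard normal earlier score Y0; a later score Y1 = r·Y0 + √(1 − r²)·e with r = 0.6 or 0.7; an event when Y1 > 1 (15.9%); and dropout probability 1/(1 + exp(−(c + b·Y0))) with b = 0.5 or 1.0 per SD and c set to give the overall dropout rate. The shift within an arm is

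Φ⁻¹(event share among those observed) − Φ⁻¹(event share among all).

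The hazard column uses only girls below the threshold at the earlier wave. Simulation at 20% dropout (3,000,000 draws):

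| r | b | Event share, all → observed | Shift, marginal (probit) | Shift, onset hazard (probit) |
|---|---|---|---|---|
| 0.6 | 0.5 | 15.9% → 14.4% | −0.065 | −0.029 |
| 0.6 | 1.0 | 15.9% → 13.0% | −0.127 | −0.047 |
| 0.7 | 0.5 | 15.9% → 14.1% | −0.076 | −0.034 |
| 0.7 | 1.0 | 15.9% → 12.4% | −0.155 | −0.057 |

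Example, second row: Φ⁻¹(0.130) − Φ⁻¹(0.159) = −1.126 − (−0.999) ≈ −0.127. At 10% dropout the ranges are about 0.03 to 0.08 (marginal) and 0.014 to 0.025 (hazard).

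**Step 4: the arm contrast.** True probit effect −0.35, r = 0.6, b = 1.0, 20% dropout, 1,000,000 girls simulated per arm:

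| Dropout depends on symptoms in | Available-case effect | Effect using the earlier score |
|---|---|---|
| both arms | −0.36 | −0.35 |
| HFPM arm only | −0.49 | −0.35 |
| control arm only | −0.22 | −0.35 |

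With the same mechanism in both arms the event rates are too low (13.0% and 6.8% against 15.9% and 8.8%), but the contrast moves by only about 0.01. With a one-arm mechanism it moves by about 0.13 to 0.14, either way.

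**The case against.** The best defence has four parts.

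- **No model is tied to WLSMV.** It appears once, conditionally, as a route to a difference test. This stands. A reader might infer that the onset and health-care-use outcomes are analysed under WLSMV. The documents do not say so: arm is a predictor in those models, not a grouping variable in a pathway comparison, and DTSA is normally fitted by maximum likelihood.
- **The article is a condensed account and refers to an SAP, not shown here, for detail.** Assigning estimators is fairly left to that document. It does not rescue the unqualified FIML sentence, which would remain wrong for any WLSMV model.
- **The size is easily overstated.** The assumptions of step 3 also lower a continuous mean by about 0.06 to 0.12 SD, and a reader might quote that as the bias in the symptom scores. That would be a mistake: continuous scores fitted by MLR are already covered by FIML. The onset hazard moves less than half as much as the marginal share. The 20% may also exceed final missingness, because up to 16 dyads (16/160 = 10%) can be replaced early in the programme.
- **MLR alone would not correct the onset models.** Full information uses only variables in the model. Girls still at risk share the same event history, and the article describes no earlier continuous score in the DTSA. This stands, and it shapes the fix.

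**Conclusion.** The conflict is real and its reach is limited. As written, the FIML statement is false for any model fitted with WLSMV, and such a model would not be protected against dropout that depends on earlier symptoms. How many models this affects cannot be determined from the article, and the number may be small.

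The size rests on assumptions outside the documents: the form and strength of the dropout mechanism, the wave-to-wave correlation, and above all a mechanism confined to one arm. Under those assumptions and 20% dropout, the shift is about 0.07 to 0.16 probit for a marginal binary outcome and 0.03 to 0.06 for an onset hazard; at 10% it is roughly half. With the same mechanism in both arms the contrast is almost unbiased.

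A reader might conclude that the plan favours HFPM. The documents do not support a direction: symptom-linked dropout in HFPM alone exaggerates the benefit, and in the control arm alone understates it. The point is worth correcting before outcome data are seen, but it does not show that the main results will be biased.

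**What to change.** In the two sections on statistical methods and missing data:

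1. State that every model with missing follow-up data is fitted by ML or MLR, with numerical integration where outcomes are categorical, and that differences between arms are tested by Satorra-Bentler or likelihood-ratio difference tests. The FIML sentence is then true for every model.
2. Include the earlier continuous symptom scores in the onset models so that full information can use them. Post-baseline scores should be modelled jointly, as auxiliary variables. If the hazard were conditioned on them, part of the arm effect would be removed.
3. Keep WLSMV with DIFFtest as a sensitivity analysis only. Alternatively, limit the FIML sentence to ML-fitted models and give each WLSMV model its own missing-data method, such as multiple imputation that includes arm and all earlier waves.

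The cost is a change of wording and longer computing time for the categorical models. No new data are needed.

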### Interim analyses

No interim analysis or stopping guidelines will be applied.

## Ethics

### Regulation statement

The study will be conducted according to the principles of the Declaration of Helsinki, current version 2008, and is in accordance with the Medical Research Involving Human Subjects Act (WMO, Sect. 4 minors), guidelines formulated in “Toetsing van onderzoek met minderjarige proefpersonen” (CCMO, 2017) and the Code of Conduct relating to expressions of objection by minors participating in medical research [110].

### Objection by minors or incapacitated subjects

The study is aimed at female adolescents of 13, 14, and 15 years of age. Parents/main caretakers have to sign a written consent, but only if their child is willing to participate. Adolescents have to sign an informed consent, in addition to their parents/main caretakers. Signed informed consent from both parents/main caretakers is crucial for participation. Participants are free to withdraw from the study at any time, without further consequences. There will be specific attention for resistance or objection to perform the assessments with minors. In case of resistance, study participation will be terminated. Examples are (1) the adolescent or/and her best friend look upset, (2) the adolescent or/and best friend end up arguing, and (3) the adolescent or/and best friend indicate that we need to stop video recording or want to end study participation. Researchers will adhere to the Code of Conduct for resistance in minors [110].

### Benefits and risks assessment, group relatedness

The burden and risks for girls associated with participation in the study are seen as minimal given that the study does in no way interfere with regular education of the girls and is focused on natural occurring interactions and activities within girls’ close friendships. The current study offers girls the opportunity to join a study focused on gaining more knowledge about the prevention of excessive co-rumination processes and internalizing problems in adolescent girls.

### Withdrawal of individual subjects

Parents/main caretakers, the girls and their best friend can withdraw from the study at any time for any reason if they wish to do so without any consequences. This is also explicitly formulated in the participant information sheet for parents/main caretakers and adolescents. It will be stressed that withdrawal from the study does not have any consequences for how they are being treated at school or elsewhere. In the case that parents/main caretakers and adolescents decide to leave the study, this means that no further information will be gathered from the adolescent and their friend from that point onwards. Data collected in previous waves will be removed upon the adolescent’ or parents’ explicit request. It is expected that withdrawal is minimal in this study because of minimal burden put onto the girls. Through good coaching by the PI and fulltime availability of the researchers, withdrawal will be minimized where possible. Dropouts will be replaced with a maximum of 16 dyads (*n* = 32), and only between T0 and the end of Phase 1 (see Fig. 1) of the prevention program. No follow-up will be conducted with subjects withdrawn from the study.

### Premature termination of the study

#### Early termination of the study

Previous studies with the PTT [22, 34] indicated that there are minimal risks of participating in the PTT. Furthermore, previous mindfulness-based studies showed minimal risks of participating in app-based mindfulness training for study purposes [111]. To be able to work skillfully with girls/dyads experiencing expected and unexpected unpleasant experiences and potential harm, we will follow the framework recommendations formulated by Baer and colleagues [112], which will be described in more detail in the following section. Therefore, no criteria are formulated for premature termination of the study.

#### Negative and serious adverse events

##### Participation in the PTT

In advance of the PTT, parents/main caretakers will be asked to stay at home during the online measurements to assist their daughter and provide support if needed. During the PTT, the trained researchers and research assistants will adhere to the Code of conduct for resistance in minors and the Observation protocol. Girls will also be told that they are free to withdraw from the task at any time, without further consequences. They will also be told that all information they share during the PTT will be treated confidentially, but that the researchers should terminate the task when there are doubts about the safety of the participants and that, in that case, parents/main caretakers or school professionals will be informed (see below for details). Girls will be informed that this will be the case when they talk about suicide, self-injury, sexual or physical abuse, substance abuse, or eating disorders during the task. Girls will be explained that this rule will prevent them from getting upset during the task. Girls will have to provide written informed consent for this part of the task separately before the task will start. In case of refusal, the PTT will not take place.

The researcher will stop the PTT immediately when the dyad starts discussing these problems and/or when the girls are clearly distressed or upset. The researcher will explain that the safety of the participants is most important and that the goal of the task is not to upset them or to discuss severe problems. The researcher will intervene by asking the girls how they are feeling, comforting them, and by offering them to take a break. If necessary, the girls can also seek comfort from their parents/main caretakers. Depending on how the girls feel after the break, the task will either be continued or terminated. This will be registered in the researcher’s logbook which is accessible across the team.

When severe problems are discussed, or when the girls got upset, the coordinating researcher will immediately (by no contact within 24 h) contact the PI. The PI will contact the independent health care professional of Youz Rijnmond in case of severe problems. Depending on the situation, parents/main caretakers of both participants of the dyad or the teacher-mentor will be informed by the PI, depending on the specific topic the dyad discussed. The Principal Investigator will inform parents/main caretakers in situations of non-family-related acute problems and will advise them to contact the family doctor or the independent health care professional. In case of severe family-related problems, the PI will call inform the teacher-mentor. We will inform the mentor in case of family-related acute problems, so that the school will be able to decide to use the Veilig Thuis Protocol. In severe cases, the Independent Health Care Professional will also be consulted by the PI.

In all situations, we protect the privacy of all participants. This implies that we only should inform parents/main caretakers or the mentor more in depth when the participant initiated the conversation about suicide, self-injury, sexual or physical abuse, or eating disorders. In these cases, the dyad will be excluded from the study. In case of resistance during the task, study participation will also be terminated. This will be the case when (1) one of the participants behaves very upset; (2) the dyad will end up arguing; or (3) one of the participants within a dyad indicate that we need to stop video recording. The dyad will be excluded from the study and parents/main caretakers will be informed by telephone. After finishing the task, participants will be told that they can contact the independent health care professional when they feel upset. We will provide the telephone number of the independent healthcare professional.

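### Parental comfort after a stopped Problem Talk Task, and the telephone call to parents when a girl is very upset, lack an exception for disclosures that may implicate someone at home

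*Protocol article*

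**What the plan says.** All the relevant rules stand in the protocol article, under Negative and serious adverse events, Participation in the PTT.

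- **Parents at home.** Before the online task, "parents/main caretakers will be asked to stay at home during the online measurements to assist their daughter and provide support if needed".
- **Topics.** Girls are told beforehand that the task will be ended over safety concerns, and that this applies "when they talk about suicide, self-injury, sexual or physical abuse, substance abuse, or eating disorders during the task". The list does not separate abuse inside the family from abuse outside it.
- **Stop rule.** "The researcher will stop the PTT immediately when the dyad starts discussing these problems and/or when the girls are clearly distressed or upset".
- **After the stop.** The researcher asks how the girls feel, comforts them and offers a break. Then: "If necessary, the girls can also seek comfort from their parents/main caretakers". The sequence closes with: "Depending on how the girls feel after the break, the task will either be continued or terminated".
- **Who is informed.** The coordinating researcher contacts the PI at once, with 24 hours as the backstop. The PI's next step depends on the topic. "The Principal Investigator will inform parents/main caretakers in situations of non-family-related acute problems". By contrast: "In case of severe family-related problems, the PI will call inform the teacher-mentor". The stated purpose of the second route is to let the school decide on the Veilig Thuis Protocol.
- **Resistance.** If a participant behaves very upset, the dyad argues, or a girl asks for the recording to stop, the dyad leaves the study and the parents are told by telephone.
- **Conduct of staff.** During the task, "the trained researchers and research assistants will adhere to the Code of conduct for resistance in minors and the Observation protocol". The Observation protocol is not among the documents at hand.

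**The concern.** The section distinguishes family-related from other problems at one point only: when the PI decides whom to inform. Two other steps can bring in a parent, and neither makes that distinction. One is comfort during the break. The other is the telephone call after a participant has become very upset.

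If a girl discloses abuse at home, the adult nearby may be the person concerned or may live with that person. A visibly shaken girl who leaves a stopped session to find a parent, or a call from the study team to that parent, may prompt questions before the PI has been reached and before the school has decided anything. The topic-based routing appears designed to avoid that order of events. The participants are 13 to 15 years old, and the study itself asks them to talk about their problems, so the order should be fixed in advance.

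**Working it through.** The plan states no figure on this point and none needs recomputing. The check sets the rules side by side.

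**1. Does the comfort step cover abuse disclosures?** The stop sentence joins two triggers, a listed severe topic and visible distress, with *and/or*. The comfort sentence follows in the same paragraph and is not restricted to either. One could read the break-and-continue sequence as meant for distress only, because an earlier sentence says the task should be terminated when safety is in doubt. That reading does not close the gap: a girl who has just disclosed abuse may well be distressed, and so falls under the second trigger anyway.

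**2. Is there an exception by topic?**

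| Step | When | Who may be involved | Family-related exception? |
|---|---|---|---|
| Comfort during the break | In the session | Parent at home, if the girl wishes | None stated |
| Contact with the PI | Immediately; 24 h backstop | PI | Not needed |
| Informing by the PI | After PI contact | Parents, or the teacher-mentor if severe and family-related | Yes |
| Telephone call after resistance | After the dyad is excluded | Parents | None stated |

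**3. Which comes first?** Parental comfort needs no hand-off. The school route needs two, from coordinating researcher to PI and from PI to teacher-mentor, before the school can decide. A parent can therefore be involved first even if everyone follows the text.

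**4. Can the resistance clause and the family route apply together?** Yes. A girl who discloses abuse at home and becomes very upset meets the condition for the teacher-mentor route and also the condition for the call to parents. The text does not say which prevails.

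**5. How many sessions are exposed?** The task is held at T0 and T4, so the plan implies 160 dyads × 2 = 320 sessions. Up to 16 replacement dyads could add up to 16 baseline sessions, giving 320 + 16 = 336. Exclusions and refusals of the separate consent for this part would lower the count. The documents give no rate of severe family-related disclosures, so no expected number is derived. Family is one of the three interpersonal topic codes under Coding process, so talk about family is foreseen; that says nothing about how often it is severe.

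**The case against.** The strongest reply is that nothing here is wrong. The comfort sentence lets a girl turn to a parent. It does not have the researcher fetch one, and it passes on no content. The routing rules govern a different act, namely whom the PI informs. Contact with the PI is immediate by default, an independent health care professional is available, and the section commits to protecting privacy in every situation. All of this stands, and it limits the point to a missing exception.

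A second reply is that in-session handling belongs in the Observation protocol, which a journal article would not reproduce. That may be so, and the exception may already be there. But the article itself states the comfort rule and the telephone rule without qualification, beside a route that is qualified. If the Observation protocol covers the case, a cross-reference settles it.

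A third reply is that parental support is usually right for a distressed adolescent, and that family-related does not mean the parent at home is implicated. This also stands. It is why the exception should be confined to disclosures that may implicate a parent or household member, and should not cover every family worry.

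A reader might infer more than the documents support:

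- **That the two rules contradict each other.** They do not. Offering comfort and formally informing are separate acts. Keeping parents out of the severe family-related route is implied by the split between the two routes and is not stated as a prohibition.
- **That the training-session rules, which mention no parental comfort, show that parents were meant to be kept out.** Those sessions are held during school hours (HFPM app-based mindfulness training program), so the silence shows nothing about intent.
- **That parents will listen in and inhibit family talk.** Being asked to stay at home for support reads most naturally as standby. The text does not place them in the room.

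**Conclusion.** The point holds as a sequencing gap in participant protection. Two steps can involve a parent without an exception for severe family-related disclosures, while the same section sends those disclosures through the PI to the teacher-mentor. As written, a parent could be involved before the PI and the school have acted. The documents do not support the claim that a parent would be involved, or that a parent would learn the content of the disclosure.

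Its weight rests on the consequence and not on frequency. Such stops are presumably rare and no rate is given. Harm further requires that someone at home is implicated, and that the girl turns to a parent or the call is made. No outcome, sample size or analysis is affected. The conclusion assumes that the Observation protocol contains no such exception, which cannot be checked here. This is worth considering as a small clarification; it is not a flaw in the trial's inference.

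**What to change.** Add one sentence to Participation in the PTT, placed so that it governs both the comfort step and the resistance clause:

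> *When the stop follows a disclosure that may implicate a parent or household member, the researcher gives comfort, does not suggest or call in a parent, and contacts the PI before closing the session; the family-related route takes precedence over the telephone call to parents.*

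If the Observation protocol already says this, a cross-reference is enough. Parental comfort stays available at every other stop, including ordinary distress about family matters, and the instruction to parents to stay at home need not change.

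The cost is one sentence and a short addition to staff training. Student research assistants conduct the recordings, so they must recognise that a disclosure may point to someone at home; the decision on whom to inform remains with the PI. In these rare cases parental support comes later. A remote researcher cannot stop a girl from going to a parent herself, so the rule fixes only what the study team does and offers.
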